#### Secondary outcomes

Ultrasound will be used to determine muscle mass on day 1 of enrolment and then weekly until day 28 or hospital discharge whichever occurs first and again at day 90 post enrolment where possible. An additional muscle mass measurement will be completed if there is no measurement scheduled within 48 h of ICU and hospital discharge. Ultrasound of leg muscularity in critically ill populations is an emerging non-invasive bedside technique that has been shown to predict muscle mass at the 3rd lumbar vertebra when quantified with computed tomography (CT) [46–48]. Measurement of muscle thickness with ultrasound is therefore a validated technique for assessment of skeletal muscle mass with good inter- as well as intra-rater reliability [46–48]. The ultrasound technique used in this protocol has been reported to be a safe and reliable measure of muscle mass [49–51]. A Philips Lumify portable ultrasound device available in the RMH ICU will be used to obtain muscle mass images. The method to obtain the images will be carried out as previously described [46, 47]. The quadriceps muscle layer thickness (QMLT) will be measured on the right side at two points; the midpoint between the anterior superior iliac spine (ASIS) and the upper pole of the patella and at the point 2/3 between the ASIS and the top of the patella. The ultrasound transducer will be held perpendicular to the skin and depth standardised at 6 cm or adjusted to visualise the femur. Three frozen images will be recorded using minimal pressure and three frozen images will be recorded using maximal pressure at each site. On screen callipers will be used to record muscle thickness and the average distance will be recorded. The upper arm muscle thickness (UAMT) will be measured on the right side at the midway point between the tip of the acromion and olecranon process [52]. Three linear still images will be taken at each landmark and recorded. Ultrasound measures will be completed on the left side if the right side is unavailable. Muscle mass measurements will be reported as change adjusted for baseline measurements [8].

Interrater reliability testing of ultrasound measures will be conducted to ensure consistency of this outcome measure. A second trained assessor will repeat the baseline land marking and image acquisition in a total of 5 patients, selected at random. In addition, interrater reliability for the quantification of muscle thickness will occur using a trained external assessor who will complete a second analysis of baseline images in 5 patients, selected at random. The muscle thicknesses for each set of images in the two subgroups will be compared [49].

Handgrip dynamometry will be used to assess muscle strength [53–55]. Handgrip dynamometry will be completed on day of enrolment and then weekly until day 28 or hospital discharge whichever occurs first and again at day 90 post enrolment. Handgrip dynamometry (Commander Echo™ Wireless Grip Dynamometer, USA or Jamar Digital Plus™, USA) will be measured in both limbs and repeated three times. Participants will be sitting in a chair or sitting at least at 45° in bed, with the patients elbow at 90° supported by a pillow or the arm of the chair. The highest measure will be recorded. An additional muscle strength measurement will be completed if there is no measurement scheduled within 48 h of ICU and hospital discharge. The highest score will be recorded.

Weight will be measured using bed scales, chair scales, hoist scales or standing scales as appropriate. Weight will be measured on day of enrolment and then weekly until day 28 or hospital discharge whichever occurs first and again at day 90 post enrolment. Weight will be reported as change adjusted for baseline.

The Subjective Global Assessment (SGA) will be used to determine the proportion of patients diagnosed with malnutrition within 48 h of hospital discharge and 90 days post enrolment adjusted for baseline nutritional status [40, 41, 53]. Those patients who have an SGA score of B (mild-moderate) or C (severe) will be classified as malnourished.

Nutrition intake from all sources including dextrose, propofol, parenteral nutrition, enteral nutrition documented in the fluid balance chart and oral intake documented in food record charts will be recorded from day of enrolment until ICU discharge and then for a total of 7 days post ICU discharge (where day of ICU discharge is defined as day 1). Energy and protein intake from all sources will be calculated by the dietitian and compared to estimated energy and protein requirements to determine nutrition adequacy over this time.

Patient-reported appetite will be assessed using visual analogue scales (VAS) [56, 57]. This will be assessed on day 28 or hospital discharge whichever occurs first and again at day 90 post enrolment.

Physical function will be assessed using the Physical Function ICU Test-Scored (PFIT-s) [58] at ICU discharge. Medical records will be retrospectively reviewed to obtain any other PFIT-s score completed over the ICU admission as part of routine care by a physiotherapist. The ICU mobility scale (IMS) [59] and modified Iowa Level of Activity (mILOA) [60] scale will be used to investigate the highest level of activity at ICU discharge and hospital discharge. The EQ-5D-5L questionnaire will be used to assess patient-rated quality of life at day 90 post enrolment [7, 61].

Computed tomography (CT) of the skeletal mass cross-sectional area will be used as an additional measure of muscle mass for a subgroup of patients who have one or more abdominal CT scans ordered as part of their medical treatment at any time over their hospital admission [46, 47]. A trained radiologist will determine if all components of the skeletal mass can be assessed at the level of L3 of an abdominal CT scan [47]. If the scan is deemed suitable, the scan will be downloaded for analysis using the Automated Muscle and Adipose Tissue Composition Analysis (AutoMATiCA) program which provides an automated analysis for skeletal muscle cross-sectional area (CSA) [46, 62]. The patients will be categorised as having low muscularity if the skeletal muscle CSA is < 110 cm^2^ for women and < 170 cm^2^ for men [63]. Changes in skeletal muscle CSA will be determined by comparing the difference between scans and the length of time this occurred over will be determined and recorded. The date of the CT scan and corresponding day of study will be recorded.

Data regarding the duration of admission, days of mechanical ventilation, any use of renal replacement therapy and highest markers of kidney function (urea and creatinine) from day of enrolment until day 28 post enrolment, hospital length of stay, in-hospital mortality and discharge destination will be collected.

All data collected by the investigator/s will be entered into an electronic database (REDCap). Data will be collected from day of enrolment until day 90.

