### Trial intervention and control

The trial intervention is β-hydroxy-β-methylbutyrate (HMB). HMB has been purchased from Myprotein (Warrington, UK). Three grams of HMB is dissolved in 150 ml of fluid. To ensure blinding of participants is maintained, orange juice is the fluid for those allowed oral intake and water for those being enterally fed. Orange juice completely masks the taste and smell of the HMB supplement. HMB powder dissolves completely in water and does not impact the viscosity of the solution. The control is 150 ml of orange juice for those allowed oral intake, or 150 ml of water for those being enterally fed. If a patient is restricted to ingesting only thickened fluids and unable to receive the intervention/control via an enteral feeding tube, Flavour Creations™ orange juice thickened to the appropriate viscosity will be used to blind the intervention/control.

Patients will receive the intervention or control from day 1 post enrolment until hospital discharge or study day 28, whichever occurs first. If a patient is readmitted to hospital within 28 days from randomisation, study procedures and administration of the intervention or control will resume. The intervention or control will be documented in the electronic medication record by the treating team and administered by the nurse caring for the patient. The number of doses prescribed and consumed will be recorded for the duration of the study. The nurse caring for the patient will document patient compliance with the intervention or control and any tolerance issues voiced by the patient believed to be associated with the consumption of trial supplement. The reason for any missed doses will be recorded.

The investigator/s, patient, nurse and member of the treating team will be surveyed on day 1 post enrolment and then day 28 or hospital discharge, whichever occurs first, as to their blinding to the intervention/control as part of the feasibility criteria. All will be invited to take their best guess of whether the participant is receiving the intervention or placebo.

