### Outcome measures

Primary and secondary outcome measures will be captured by trained study investigator/s. Summary study schedule and outcome measures are detailed in Table 2. Any outcome data for weight, nutrition status, appetite, muscle mass, muscle strength or physical function, collected within ± 48 h of the specified time points from day 0 to day 28 will be used for this feasibility study. For practical reasons, it may not always be possible for patients to return to hospital on the exact 90-day follow-up time point. Therefore, any data collected within a 2-week window of the “90 day” follow-up measure will be used, and date of measure recorded.

**Table 2 Tab2:** Study schedule and outcome measure

	Assessment/Procedure	Screening and enrolment (day 0)	Day 1, then weekly until day 28 or hospital D/C	Daily from day 1–day 28 or hospital D/C	Day 1	Day 0 until ICU D/C and then 7 days post ICU D/C	ICU D/C	Day 28 or hospital D/C	Day 90 post enrolment
**Study procedures**	Informed consent	**X**							
	Demographic data, APACHE II, ANZROD and ISS, baseline creatinine and urea	**X**							
	Anthropometric data (weight, height and BMI)	**X**							
	Body weight		**X**						**X**
	Nutrition status (SGA)	**X**						**X**	**X**
	Muscle mass		**X**						**X**
	Handgrip strength		**X**						**X**
	Physical function (IMS and mILOA)						**X**	**X**	
	Physical function (PFIT-s)						**X**		
	Patient-reported appetite		**X**						**X**
	Nutrition intake					**X**			
	Administration of intervention/control			**X**					
	Blinding survey				**X**			**X**	
	ICU LOS, days of mechanical ventilation, hospital LOS, discharge destination, use of renal replacement therapy, highest creatinine and urea							**X**	
	Quality of life survey								**X**
	Place of residence and employment status	**X**							**X**
	Mortality							**X**	**X**

*ANZROD* Australian and New Zealand Risk of Death score, *APACHE II* Acute Physiology, Age, Chronic Health Evaluation II, *BMI* body mass index, *IMS* ICU Mobility Scale, *ISS* Injury Severity Scale, *LOS* length of stay, *mILOA* modified Iowa Level of Activity, *PFIT*-*s* Physical Function ICU Test-Scored, *SGA* Subjective Global Assessment

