### Management of adverse events

It is not anticipated that any adverse events will occur in relation to the study protocol. If any adverse events do present, the nature, severity, causality and course of the adverse event will be recorded. All adverse events will be recorded from the time of consent; any event will be discussed with the attending Intensivist or Trauma consultant. Any serious adverse events related to the study will be reported by the investigator to the Melbourne Health Human Research and Ethics Committee within 24 h of site personnel becoming aware of it.

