### Analysis plan

Baseline variables including demographics, severity of illness, ICU and hospital length of stay, mortality and nutritional markers will be reported according to the two randomised groups. Differences between the two treatment groups will be reported for the multiple parameters of interest, including change in weight, muscle mass and muscle strength from baseline to day 28 or hospital discharge. As well, the intraclass correlation coefficient (ICC) and coefficient of variation (CV) will be used to summarise interrater reliability of the ultrasound measurements.

Selected differences among these parameters of interest will be compared between randomised groups using the two-sample unpaired *t* test for approximately normal data, the Wilcoxon-rank sum test for substantially skew data and the Fisher’s exact test for categorical variables within contingency tables as appropriate. As well, exploratory multivariable models may be generated, incorporating adjustment for initial baseline values and other selected potentially relevant co-variables using linear regression. Results will be reported with 95% confidence intervals to aid in the interpretation of results in the context of pilot data.

Given the illness severity of the trauma patients under study, deaths during the study are likely, making the outcomes often only practically ascertainable in survivors. In the presence of sufficient data, exploratory time-to-event analyses in competing-risks regression models may be applied to return the subhazard functions of failure events of primary interest whilst accounting for the competing outcome of death using the method of Fine and Gray [66]. Multiplicity of testing will be acknowledged but multiple statistical tests will be otherwise unadjusted, consistent with the exploratory nature of this pilot study. Data analyses will be carried out using recent versions of established statistical software packages, which at the time of writing include the Statistical Package for the Social Sciences (IBM® SPSS® Statistics) and Stata (Stata Statistical Software. College Station, TX: StataCorp LP; 2019).

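### The window for highest creatinine and urea and for renal replacement therapy opens on day 0, before the first dose, so pre-dose data can be recorded as outcome (minor)

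*Protocol article*

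**What the plan says.** The protocol article, Secondary outcomes, lists among the data to be collected "any use of renal replacement therapy and highest markers of kidney function (urea and creatinine) from day of enrolment until day 28 post enrolment". The same sentence covers duration of admission, ventilation days, length of stay, in-hospital mortality and discharge destination.

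Table 2 (Outcome measures) labels screening and enrolment as day 0 and places "Demographic data, APACHE II, ANZROD and ISS, baseline creatinine and urea" in that column. The row containing "use of renal replacement therapy, highest creatinine and urea" is marked only in the column for day 28 or hospital discharge.

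Trial intervention and control fixes the start of exposure: "Patients will receive the intervention or control from day 1 post enrolment until hospital discharge or study day 28, whichever occurs first".

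The Analysis plan says that "exploratory multivariable models may be generated, incorporating adjustment for initial baseline values" and does not name the kidney markers. Adverse events are handled separately: "All adverse events will be recorded from the time of consent".

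**The concern.** An outcome meant to reflect what happens under treatment should be measured after treatment starts. Here the window for the maximum opens one study day before the first dose and contains the baseline value itself. In patients whose creatinine or urea is high soon after injury and then falls, the recorded outcome is a number that neither supplement nor control could have influenced.

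The same applies to renal replacement therapy. Table 1 requires two full calendar days in ICU, allows consent up to 7 days after injury, and does not exclude patients already on this therapy. It can therefore be running at enrolment. An item that records any use from day 0 merges those patients with patients who start therapy after dosing.

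This is a data-capture definition. If only one baseline, one maximum and one any-use item are stored, later analysis cannot recover the timing. The results are intended to inform a larger trial, so a blurred summary would be carried forward.

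**Working it through.** The document gives no figure to reproduce: there is no effect size, SD or event rate for the kidney markers, and the 50 participants rest on recruitment feasibility. The check compares the timing statements, works through the arithmetic of the maximum, and then gives two illustrations with assumed inputs.

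**1. Timing.**

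| Item | Starts | Where stated |
|---|---|---|
| Baseline creatinine, urea | day 0 | Table 2 |
| Window for highest value and therapy | day of enrolment = day 0 | Secondary outcomes; Table 2 |
| Supplement or control | day 1 | Trial intervention and control |

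The outcome window contains the baseline day. Recorded maximum M = max(B, P), where B is the day 0 value and P the post-dose maximum. Hence M/B = max(1, P/B), which is never below 1.

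**2. What is lost and what is not** (hypothetical values, same units throughout).

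| Day 0 / nadir / later peak | M | M/B | Rise from nadir |
|---|---|---|---|
| 180 / 80 / 140 | 180 | 1.00 | 140/80 = 1.75, hidden |
| 180 / 80 / none (stays at 80) | 180 | 1.00 | none |
| 180 / 80 / 220 | 220 | 220/180 = 1.22 | visible |
| 80 / 70 / 150 | 150 | 150/80 = 1.88 | visible |

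The first two patients cannot be told apart. A rise above day 0 is always seen; only a rise ending at or below day 0 is lost.

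**3. Illustration without a daily course (all inputs assumed).** Let X = log(P/B) be normal with mean m and SD s = 0.3 in controls, and let treatment raise P by 20% (log 1.2 = 0.182). Then E[max(0, X)] = mΦ(m/s) + sφ(m/s), and day 0 is the highest value in a share Φ(−m/s) of controls. For m = 0, controls give 0.3 × 0.399 = 0.120. The treated arm gives 0.182 × 0.728 + 0.3 × 0.332 = 0.232. The observed ratio is exp(0.232 − 0.120) = 1.12.

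| m | Share with day 0 highest | Observed ratio (true 1.20) |
|---|---|---|
| +0.3 | 16% | 1.18 |
| +0.1 | 37% | 1.14 |
| 0 | 50% | 1.12 |
| −0.1 | 63% | 1.09 |
| −0.3 | 84% | 1.05 |

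The documents do not give this share, so no row can be preferred.

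**4. Illustration with a daily course (all inputs assumed).** 25 per arm, log-creatinine SD 0.4, measurement noise 0.08, 14 daily values, 20% to 80% of patients recovering by 0.3 or 0.7 log units, and a 1.2- or 1.5-fold rise on treatment from day 7. Day 0 was the maximum in 0.2% to 79% of treated patients. Across the scenarios the between-arm ratio was 1.03 to 1.42 with day 0 included and 1.04 to 1.45 with it excluded. The gain within a scenario ran from nothing (1.130 both ways) to 1.276 against 1.379. Excluding day 0 helps only in part, because the first post-dose values of a recovering patient still set the maximum.

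Power of a t test on log(maximum/baseline) moved both ways when day 0 was dropped: from 0.451 to 0.734 in one scenario and from 0.923 to 0.509 in another. A plain ratio to baseline then also carries the spread in recovery between patients.

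**5. Renal replacement therapy.** Table 1 has no exclusion for it, Table 2 has no day 0 entry for it, and the end-of-stay item records use since enrolment. As described, existing and new therapy give the same entry. The documents give no prevalence at enrolment, so this part has no size.

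**The case against.** The strongest reply is that little depends on this item. No section calls creatinine, urea or renal replacement therapy a safety outcome, and no renal hypothesis is stated. The Analysis plan names weight, muscle mass and muscle strength, and commits to no test of the kidney markers. The primary outcomes are blinding, recruitment and retention, and doses consumed, and the window touches none of them. The baseline is recorded, so every rise above it can be seen. Randomisation balances day 0 values in expectation, so neither arm is favoured. A condensed article may also omit start dates that the case report form holds. All of this stands, and it sets the severity.

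It does not remove the point. As long as the maximum includes day 0, dividing it by baseline cannot separate a patient who recovered from one who recovered and then rose again. The wording as published fixes what is captured.

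A reader might infer more than the documents support:

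- That these markers are the trial's only safety data. Adverse events are recorded from consent, although that does not guarantee that a creatinine rise is captured.
- That the trial would pass on a false finding of no renal effect. That presumes a between-arm comparison to which the plan does not commit.
- That a true ratio of 1.20 would be reported as 1.05. That figure needs day 0 to be the highest value in 84% of controls and a model without a daily course.
- That marker values should also be cut off when renal replacement therapy starts. That is a debatable trade-off which brings informative censoring of its own.

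**Conclusion.** The point holds as a minor one. The windows for the kidney markers and for renal replacement therapy open before exposure, although a separate baseline exists. A rise on treatment that ends at or below the day 0 value is invisible, and therapy already running at enrolment is not distinguished from new therapy.

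The consequence is dilution of a minor exploratory outcome, without expected direction between the arms. Its size cannot be estimated from the documents: it depends on how often day 0 is the peak, which the assumed scenarios leave anywhere from 0.2% to 79% of treated patients. The conclusion rests on reading enrolment as day 0 and first dosing as day 1, which Table 2 and the intervention section both support.

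**What to change.** In Secondary outcomes and Table 2:

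- Define the markers as the highest creatinine and the highest urea after the first dose up to day 28, reported against the day 0 baseline already collected.
- Add renal replacement therapy status to the day 0 column, and report therapy newly started after the first dose separately from therapy already running.

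The cost is a wording change and one extra date or flag in the database. The highest of the baseline and post-dose values can still be computed from the two stored values, so that summary is not lost.

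The limits should be stated with the change. In the first example above, the post-dose maximum gives 140/180 = 0.78 against 80/180 = 0.44 for the patient who stays low. The two are then separated, but the 1.75-fold rise still appears as a fall from baseline. If an early post-dose value on the way down exceeds 140 in both patients, they may again be hard to tell apart. Participants on therapy at day 0 contribute no new-onset event. The reason for the change is that the outcome becomes a post-dose quantity; a gain in power is not assured.

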### Management of adverse events

It is not anticipated that any adverse events will occur in relation to the study protocol. If any adverse events do present, the nature, severity, causality and course of the adverse event will be recorded. All adverse events will be recorded from the time of consent; any event will be discussed with the attending Intensivist or Trauma consultant. Any serious adverse events related to the study will be reported by the investigator to the Melbourne Health Human Research and Ethics Committee within 24 h of site personnel becoming aware of it.

### Withdrawals

A participant (or his/her surrogate decision maker) may choose to withdraw at any stage by choice or if they experience an adverse event. If at any time the attending consultant feels that the intervention or control oral supplement is inappropriate for the patient, the patient can be withdrawn from the study. Any patient who is withdrawn from the study will not be replaced.

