#### Primary outcomes

The feasibility of administering the intervention or control will be quantified as:Successful blinding of the intervention determined through patient and clinician surveysRecruitment and retention rates analysed for patients who meet all inclusion and none of the exclusion criteriaThe amount of HMB supplementation actually consumed compared to the amount intended with full protocol compliance

The following feasibility indicators will be reported:Percentage of surveyed clinicians are able to correctly identify the interventionPercentage of patients who meet all of the inclusion and none of the exclusion criteria are recruited and % of enrolled patients retained until hospital discharge; andPercentage of the prescribed HMB supplementation doses consumed

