### Sample size

To our knowledge, this will be the first study to report feasibility of HMB administration to critically ill trauma patients. Therefore, data will be used to generate sample size estimates for later confirmatory studies [64, 65]. For this trial, a suitable number of participants has been estimated based on admission data at the host institution. A recent observational study was able to recruit 28 patients over a 6-week period using a similar eligibility criteria [4]. Accounting for attrition associated with obtaining written informed consent, it is estimated to be feasible to recruit 50 participants over a 18-month period [65]. If participant recruitment is significantly less than this, the study can be extended for an additional 6–12 months.

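### The withdrawal rule lets a judgement about the supplement take the patient out of the study, so an adherence problem can be counted as a retention failure and later outcomes may be lost

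*Protocol article*

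**What the plan says.** The Withdrawals section gives two ways out of the trial. The first belongs to the participant or surrogate, who "may choose to withdraw at any stage by choice or if they experience an adverse event". The second belongs to the attending consultant: if that doctor "feels that the intervention or control oral supplement is inappropriate for the patient, the patient can be withdrawn from the study". The section closes with "Any patient who is withdrawn from the study will not be replaced". It describes no status in which the supplement has stopped but the patient is still followed.

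Elsewhere the article treats taking the supplement and staying in the trial as different things. Under Primary outcomes, one indicator is the percentage "of enrolled patients retained until hospital discharge"; another is the percentage of prescribed HMB doses that were consumed. Under Trial intervention and control, doses prescribed and consumed are recorded, and "The reason for any missed doses will be recorded".

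On follow-up and analysis, the last sentence of Secondary outcomes says "Data will be collected from day of enrolment until day 90". The Analysis plan says "Selected differences among these parameters of interest will be compared between randomised groups". The Sample size section says that "data will be used to generate sample size estimates for later confirmatory studies".

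**The concern.** Stopping a study product and leaving a study are different events. The first concerns exposure and the second concerns whether outcomes can be observed. The consultant rule joins them: a view about the product can end participation.

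Three of the trial's own aims are affected.

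- **Retention.** A patient withdrawn before hospital discharge because the supplement was judged unsuitable counts as not retained, although that patient might have been willing and able to attend every assessment. The planners of the later trial would then see a follow-up problem where there was an adherence problem.
- **Adherence.** A withdrawn patient would presumably have no further doses prescribed. The percentage of prescribed doses consumed could then miss the most complete form of non-adherence. The Primary outcomes section also mentions the amount intended under full compliance, which would not shrink in this way; having two denominators makes a clear rule more useful.
- **Outcome estimates.** The Study objectives include learning whether weekly and day-90 measures can be obtained, how far mortality is a competing risk, and what effect size and variance to expect for muscle mass. All three need data from patients who stop the supplement. If those patients differ from the rest and stopping differs by arm, an analysis of the remaining patients is no longer a fair comparison of the groups as randomised.

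**Working it through.** **No stated figure to reproduce.** The article gives no withdrawal rate, outcome SD or retention target, and the 50 participants rest on recruitment feasibility. The withdrawal numbers and outcome gaps below are therefore assumptions, shown as ranges. From the article come only N = 50 and 1:1 allocation, that is 25 per arm.

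**1. Effect on the retention indicator.** Retention = (50 − w − m)/50, where w is the number withdrawn only because the supplement was judged inappropriate and m is the number lost for other reasons. If the w patients stopped the supplement but stayed in follow-up, retention would be (50 − m)/50.

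| w (assumed) | m (assumed) | Retention under the rule | Retention if kept in follow-up | Difference (points) |
|---|---|---|---|---|
| 2 | 0 | 48/50 = 96% | 100% | 4 |
| 5 | 0 | 45/50 = 90% | 100% | 10 |
| 10 | 0 | 40/50 = 80% | 100% | 20 |
| 2 | 5 | 43/50 = 86% | 90% | 4 |
| 5 | 5 | 40/50 = 80% | 90% | 10 |
| 10 | 5 | 35/50 = 70% | 90% | 20 |

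For 40/50 the Wilson 95% confidence interval is 67% to 89%. The shift is w/50 whatever the other losses, and it does not depend on any difference between arms.

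**2. Effect on precision, if outcomes are lost.** The 95% CI half-width for a difference in means, in SD units, is 1.96 × √(2/n), with n per arm and losses spread evenly.

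- n = 25: 1.96 × √(2/25) = 0.55 SD
- n = 24 (2 lost): 0.57 SD
- n = 22.5 (5 lost): 0.58 SD
- n = 20 (10 lost): 0.62 SD

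**3. Effect on the group difference, if outcomes are lost and stopping differs by arm.** Let a share p of one arm be withdrawn, with mean outcome δ worse than those in that arm who continue. The full-arm mean is then the continuers' mean minus pδ, so analysing continuers only flatters that arm by pδ.

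| p, one arm only (assumed) | δ = 0.5 SD | δ = 1.0 SD |
|---|---|---|
| 4% (1 of 25) | 0.02 SD | 0.04 SD |
| 10% | 0.05 SD | 0.10 SD |
| 20% (5 of 25) | 0.10 SD | 0.20 SD |

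If p and δ are the same in both arms, the two biases cancel (pδ − pδ = 0), but the loss in step 1 remains.

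**The case against.** The strongest reply is that the text says less than it might seem to, and that several stronger readings fail.

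- A reader might infer that such patients must leave the study. The wording is permissive, and nothing forbids stopping the supplement while follow-up goes on. This stands. It does not remove the problem: with no supplement-only status defined, similar patients may be classed as non-adherent or as not retained according to the consultant's choice.
- A reader might infer that an adverse event ends participation. It does not. That sentence describes the participant's or surrogate's own choice, and the point here does not rest on it.
- A reader might infer that outcomes after withdrawal are certainly lost. That is the plain meaning of leaving a study, but the article does not state it. The general sentence on data collection to day 90 makes no exception for withdrawn patients, and equally does not say that they are covered. The full protocol may say more.
- The Analysis plan compares groups as randomised and does not exclude withdrawn patients. This stands, but an analysis rule cannot supply data that were not collected.
- Adherence and retention are already separate indicators, and a patient can miss doses and remain in the study. The overlap is thus confined to patients whom a consultant withdraws.
- Treating doctors are blinded, the article says that orange juice fully masks taste and smell, and no adverse events are anticipated. Strongly differential stopping is therefore less likely, though tolerance could still differ by arm. That stopped patients are sicker is plausible but is not established in the article.
- The muscle comparisons are secondary and exploratory, no retention threshold is set, and even a bias of 0.20 SD lies well inside the half-width of 0.55 SD with all 50 patients. This limits the weight of step 3. It does not touch step 1.

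**Conclusion.** The point holds in a limited form. The article states a rule by which a judgement about the supplement may end study participation, and it offers no way to stop the supplement and stay in follow-up. This is a stated rule that is badly fixed, not a detail left to another document.

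The firmest consequence is for retention, a primary feasibility indicator: 4 to 20 percentage points lower if 2 to 10 of 50 patients were withdrawn this way. That needs only that the rule be used before hospital discharge. Loss of later muscle, strength, day-90 and mortality data is possible. Bias in the exploratory comparison, about 0.02 to 0.20 SD, further requires that outcomes are lost, that stopping is confined to one arm (4% to 20%) and that stopped patients do 0.5 to 1.0 SD worse than those who continue. The article supports none of these rates. A larger claim, such as a bias of 10 × (0.20 − 0.05) = 1.5 percentage points of muscle loss in favour of HMB, is correct arithmetic on rates and a gap that have no source in the article, and it should not be read as an expected effect.

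The wording should be corrected, but the trial is not invalid without the correction.

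**What to change.** Reword the Withdrawals section around two defined states.

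1. **Discontinued study supplement.** This applies when the consultant judges the supplement inappropriate. Scheduled assessments and mortality follow-up continue to day 90, and the patient is analysed in the group as randomised.
2. **Withdrawn from follow-up.** This applies only when the participant or surrogate withdraws consent to data collection.

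Report the two counts separately by arm, with reasons: the first under adherence, the second under retention. State also which denominator the dose indicator uses once the supplement has been stopped. The decision on when to stop the supplement stays with the clinician and is not changed by this wording.

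The cost is a short amendment and some extra follow-up work for the patients concerned. The assessments are those already scheduled in Table 2, so no new measurement is needed.
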